**2.21 Will this research study be conducted within a nursing home located in Pennsylvania?**

No.

### **3.0 – Human Subjects**

#### **3.1 What is the age range of the subject population?**

Age 21 and above

#### **3.2 What is their gender?**

Both males and females.

#### **3.3 Will any racial or ethnic subgroups be explicitly excluded from participation**

No

#### **3.4 For studies conducted in the U.S., do you expect that all subjects will be able to comprehend English?**

Yes.

#### **3.5 Participation of Children: Will children less than 18 years of age be studied?**

No.

#### **If No, provide a justification for excluding children.**

Based on a review of the age distribution of patients admitted for HF at our study hospitals (youngest ~mid-30's) and our R34 HF pilot data, we do not expect to encounter any child or adolescent patients (age < 21) on the adult inpatients wards where we plan to conduct our enrollment procedures. Furthermore, given the outlier status these participants would present, we will exclude children and adolescents from our protocol.

#### **3.6 Does this research study involve prisoners, or is it anticipated that the research study may involve prisoners?**

No.

#### **3.7 Will pregnant women be knowingly and purposely included in this research study?**

No.

#### **3.8 Does this research study involve neonates?**

No.

#### **3.9 Fetal Tissues: Does this research involve the use of fetal tissues or organs?**

No.

**3.10 What is the total number of subjects to be studied at this site, including subjects to be screened for eligibility? Note: The number below is calculated by summing the data entered in question 3.11. Any additions or changes to the values entered in 3.11 will be reflected in 3.10.**

4500

**3.11 Identify each of the disease or condition specific subgroups (include healthy volunteers, if applicable) that will be studied.**

1) how many subjects will undergo research related procedures at this site; and

2) if applicable, how many subjects will be required to undergo screening procedures (e.g., blood work, EKG, x-rays, etc.) to establish eligibility. Do Not include subjects who will undergo preliminary telephone screening.

| Subgroup | Number to undergo research procedures | Number to undergo screening procedures |             |
|----------|---------------------------------------|----------------------------------------|-------------|
| Control  | 125                                   | 750                                    | 125
750  |
| eUC      | 250                                   | 1500                                   | 250
1500 |
| UC       | 125                                   | 750                                    | 125
750  |
| Blended  | 250                                   | 1500                                   | 250
1500 |

**3.12 Provide a statistical justification for the total number of subjects to be enrolled into this research study at the multicenter sites or this site.**

If applicable, refer to the statistical section in the clinical protocol or grant. Specify the page numbers in the textbox. See C13a-f in our grant application.

**3.13 Inclusion Criteria: List the specific criteria for inclusion of potential subjects.**

1. Systolic heart failure (documented ejection fraction  $\leq 40\%$ ).
2. HF symptoms meeting criteria for New York Heart Association (NYHA) classes II, III or IV.
3. Inpatient PHQ-2 screen-positive for depression; or PHQ-2 screen negative for depression and PHQ-9  $<5$  if non-depressed control.
4. PHQ-9  $\geq 10$  when reassessed two-weeks following hospital discharge, or PHQ-9  $<5$  if non-depressed control.
5. No cognitive impairment (as documented in the record, use of donepezil or similar medications for treating cognitive impairment, or the MoCA).
6. Able to be evaluated and treated for depression as an outpatient.
7. English speaking, not illiterate, or possessing any other communication barrier.
8. Have a household telephone.

**3.14 Exclusion Criteria: List the specific criteria for exclusion of potential subjects from participation.**

1. Receiving active treatment for a mood or anxiety disorder from a mental health specialist.
2. Unstable medical condition as indicated by history, physical, and/or laboratory findings.
3. Presence of non-cardiovascular conditions likely to be fatal within 12 months (e.g., cancer).
4. Organic mood syndromes, including those secondary to medical illness or drugs.
5. Active suicidal ideation.
6. Current or history of psychotic illness according to DSM-IV criteria.
7. Current or history of bipolar illness according to patient self-report, past medical history, and DSM-IV criteria.
8. Current alcohol or other substance abuse as evidenced by chart review and the AUDIT-C questionnaire.
9. Age  $\leq$  21 years.

**3.15 Will HIV serostatus be evaluated specifically for the purpose of participation in this research study?**

No.

**4.0 – Subject Recruitment and Informed Consent Procedures**

**4.1 Select all recruitment methods to be used to identify potential subjects:**

Waiver of informed consent to review medical records ONLY for the identification of potential subjects.

Advertisements.

**4.2 Provide a detailed description of your recruitment methods, including identifying and initiating contact with participants:**

As described earlier in this IRB application, each UPMC hospital has an inpatient HF Management Program that HF patients are referred to automatically upon hospital admission through an automated review of their admitting diagnoses, or following admission should the HF diagnosis be uncovered during the hospitalization. Our nurses will be notified by the house staff of these patients, upon which the study nurses will confirm the patient's ejection fraction. If it is  $>40\%$ , then the nurses will ask the house staff to get that patient's permission to approach. If the patient agrees to be approached our study nurse will then explain our study, and after obtaining verbal consent, will assess the patient for the described eligibility criteria prior to hospital discharge. If the patient is not interested in our study, we will only collect his or her data as required by our funding organization (age, EF, race, gender).

**4.6 Are you requesting a waiver to document informed consent for any or all participants, for any or all procedures? (e.g., a verbal or computerized consent script will be used, but the subjects will not be required to sign a written informed consent document, such as with phone screening. This is not a waiver to obtain consent.**

Yes

**4.6.1 Identify the specific research procedures and/or the specific subject populations for which you are requesting a waiver of the requirement to obtain a signed consent form. If not all, identify the specific procedures and/or subject populations for which you are requesting a waiver:**

We request a waiver of signed consent for our study nurses to determine whether they may later be eligible to provide written informed consent to participate in our clinical trial. Our nurses will briefly describe the study, and if they patient is interested, they will establish eligibility (e.g., having a telephone, no history of severe mental illness), and administer the PHQ-2, NYHA questions, to establish if the patient indeed meets criteria for our study. We will also ask the patient their sex and race in order to be able to report these data to our funding agency. Finally we will administer the Montreal Cognitive Assessment to establish that eligible patients will be able to understand the study consent document, Data collected during this screening will be de-identified, assigned a unique subject ID number, and stored electronically on a password protected laptop.

**4.6.2 Indicate which of the following regulatory criteria is applicable to your request for a waiver of the requirement to obtain a signed consent form.**

45 CFR 46.117(c)(2)

45 CFR 46.117(c)(1) That the only record linking the subject and the research would be the consent document and the principal risk would be potential harm resulting from a breach of confidentiality. Each subject will be asked whether the subject wants documentation linking the subject with the research, and the subject's wishes will govern; or

45 CFR 46.117(c)(2) That the research presents no more than minimal risk of harm to subjects and involves no procedures for which written consent is normally required outside of the research context.

**4.6.2.1 Address why the specific research procedures for which you are requesting a waiver of the requirement to obtain a signed consent form present no more than minimal risk of harm to the research subjects:**

There are no physical or psychological risks associated with this research activity, and patients can decline to participate in our screening procedure and later in the trial at any time. The questions we propose to ask them are similar to those questions asked upon scheduling them for a medical or psychiatric clinic visit.

**4.6.2.2 Justify why the research listed in 4.6.1 involves no procedures for which written informed consent is normally required outside of the research context:**

HF patients who are suspected to have developed symptoms of depression are routinely screened with the PHQ-2 and PHQ-9 as recommended by an American Heart Association Science Advisory. Therefore, our screening questions are not additional burden to the patient, and should be administered in routine care.

**4.6.3 Address the procedures that will be used and the information that will be provided (i.e., script) in obtaining and documenting the subjects' verbal informed consent for study participation:**

The recruiter will briefly explain the purpose of the research study and ask the subject if they are interested. The answer will be documented in our paperless data entry system which will

also guide the recruiter through the remainder of the screening process. (Screening Script attached in IRB form).

**4.7 Are you requesting a waiver to obtain informed consent or an alteration of the informed consent process for any of the following?**

Yes.

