### **1.2 Specific Aims: List the goals of the proposed study.**

Specific Aims are to: (1) evaluate the effectiveness of a telephone-delivered “blended” collaborative care intervention for treating both depression and HF that could be readily adopted into routine clinical practice if proven effective; and (2) advance our understanding of the moderators and mediators of depression treatment on clinical outcomes.

We propose to screen hospitalized adults with HF for depression and then randomize 625 protocol-eligible patients with a cardiac ejection fraction (EF)  $\leq 40\%$ , New York Heart Association (NYHA) class II-IV symptoms, and who have at least a moderately elevated level of depressive symptoms (PHQ-9  $\geq 10$ ) at two-weeks following hospital discharge to a 12-month course of either: (1) Collaborative care for treating both HF and depression (“blended”); (2) Collaborative care for treating HF alone (enhanced usual care (eUC)); or (3) Their doctors’ “usual care” for treating HF and depression (UC).

Additionally, we will enroll 125 non-depressed HF patients to better evaluate the benefits derived from treating depression and, together with UC, control for any secular changes in the management of HF as elements of the 2010 Affordable Care Act are phased-in (Total N=750). Our co-primary hypotheses will test whether “blended” collaborative care can produce at 12-months follow-up a: (A) moderate 0.50 effect size (ES) or greater improvement in HRQoL vs. UC; and (B) clinically meaningful 0.30 ES or greater improvement in HRQoL vs. eUC. Our secondary hypotheses will evaluate in comparisons with eUC and UC the effects of our “blended” intervention on mood, functional status, delivery of and adherence with guideline-consistent care, incidence of cardiovascular events, health care utilization, and costs.

Though not explicit objectives of this application, the proposed trial will also serve as the basis for ancillary studies to examine the genomic moderation of treatment effects and such mediating mechanisms as blood pressure control, sleep quality, and chronic inflammation to further advance our understanding of how depression and its treatment affects clinical outcomes.

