12. Has no current alcohol or other substance abuse as evidenced by chart review and the AUDIT-C questionnaire.
13. Is age  $\geq$  21 years old.

This will take up to 30 minutes. If the patient answers "no" to both items and scores  $<4$  on the PHQ-9 indicating an absence of mood symptoms and wishes to continue, they will be randomly sampled to participate in our non-depressed comparison cohort (see Figure 1 in grant application). All PHQ-2 (+) patients will receive their doctors' "usual" post-discharge medical care and a copy of the NIMH brochure entitled "Depression and Heart Disease" or a similar pamphlet, to destigmatize depression, increase awareness of the condition, and briefly describe treatment options. Regardless of whether the patient later agrees to enroll into our study. At 2-weeks following hospital discharge, a member of our study team will recontact the patient via telephone to confirm eligibility criteria and administer the PHQ-9. For PHQ-2 (+) patients we will

require a PHQ-9 score of 10 or higher to continue in our protocol; and for PHQ-2 (-)/PHQ-9 <5 patients, we will require a PHQ-9 <5 to continue in our non-depressed comparison cohort.

**2.5.2 What steps will be taken in the event that a clinically significant, unexpected disease or condition is identified during the conduct of the screening procedures?**

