- **who from the research team will be involved in the consent process (both the discussion and documentation);**
- **person who will provide consent or permission;**
- **information communicated; and**
- **any waiting period between informing the prospective participant about the study and obtaining consent**

Each UPMC hospital has an inpatient HF Management Program that HF patients are referred to automatically upon hospital admission through an automated review of their admitting diagnoses, or following admission should the HF diagnosis be uncovered during the hospitalization. Our study cardiologist, [name], will encourage HF Management Program staff and cardiology consult teams to obtain patients' whose ejection fraction is  $\leq 40\%$  to provide verbal HIPAA agreement permitting our nurse-recruiters to confirm their ejection fraction meets study criteria, and if so to approach and explain our study and obtain their patients' consent to undergo our screening procedures. Our study nurses will then screen the patients for eligibility as described in 4.2. If the patient meets eligibility criteria for our study, and remains interested, the study nurse will then explain the study in detail as outlined in the

consent document, answer any questions the patient may have, and give the patient time to consider participation or discuss it with his/her family. If the patient agrees to participate, then they will be asked to sign the informed consent, and the study nurse will document the process. At 2-weeks after hospital discharge a research assessor will call the patient, and establish if the patient is still eligible. At this point the patient can also decide to continue to participate in our study. Only if the patient is still eligible and confirms his continued interest, will he/she be randomized to our study.

**4.13 Are you requesting an exception to either IRB policy related to the informed consent process? For studies involving a drug, device or surgical procedures, a listed physician investigator is required to obtain the written informed consent unless an exception to this policy has been approved by the IRB For all other studies, a listed investigator is required to obtain consent (Note: In order to request an exception to this policy, the study must be minimal risk).**

Yes

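### Section 4.2 states the ejection-fraction gate for approaching patients in the wrong direction (>40% instead of ≤40%), and section 2.5.1 gives two inpatient PHQ-9 cut-offs for the non-depressed cohort

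*Protocol*

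**What the plan says.** **Ejection fraction.** Four places give the threshold.

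- Section 1.2 (Specific Aims) describes the patients to be randomised as those "with a cardiac ejection fraction (EF) $\leq 40\%$ , New York Heart Association (NYHA) class II-IV symptoms".
- Section 3.13, item 1, reads "Systolic heart failure (documented ejection fraction $\leq 40" (per cent). The item has no separate version for the non-depressed controls.
- Section 4.12 (consent process) has programme staff turn to patients "whose ejection fraction is $\leq 40\%$ to provide verbal HIPAA agreement permitting our nurse-recruiters to confirm their ejection fraction meets study criteria". Approach follows only if the criterion is met.
- Section 4.2 (recruitment methods) has the study nurses confirm the EF and then sets the condition ">40\%$ , then the nurses will ask the house staff to get that patient's permission to approach". Patients who agree then have the study explained and are assessed for eligibility.

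**PHQ-9 for the non-depressed cohort.** Section 2.5.1 first describes PHQ-2-negative inpatients who score below 4 "on the PHQ-9 indicating an absence of mood symptoms and wishes to continue"; these are sampled for the comparison cohort. Later in the same section the group is labelled PHQ-2 negative with PHQ-9 below 5, and for the two-week call the text says "we will require a PHQ-9 <5 to continue in our non-depressed comparison cohort". Section 3.13 uses below 5 both for the inpatient screen (item 3) and for the two-week reassessment (item 4).

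**The concern.** Section 4.2 answers the form's question about how participants are identified and first contacted, so its threshold is a working instruction and not background. It is the reverse of the inclusion criterion. The EF gate governs entry for every participant, depressed or not, in a trial that plans to screen 4,500 patients (section 3.10). A recruiter or programmer who worked from 4.2 alone would approach ineligible hospitalised patients and pass over eligible ones.

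The PHQ-9 mismatch is a lesser matter of the same kind. Two cut-offs are given for one screen at one time point, so who may enter the comparison cohort depends on which line is followed. Section 1.2 gives that cohort a role in judging the benefit of treating depression, so its definition should be unambiguous.

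**Working it through.** No formula applies, because no sample size, power, event count or alpha is involved. The check sets the stated thresholds side by side.

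| Item | Section | Rule as written |
|---|---|---|
| EF | 1.2 | ≤40% |
| EF | 3.13 item 1 | ≤40% |
| EF | 4.12 | ≤40% |
| EF | 4.2 | >40% |
| Inpatient PHQ-9, non-depressed | 2.5.1, first mention | <4 |
| Inpatient PHQ-9, non-depressed | 2.5.1, later label | <5 |
| Inpatient PHQ-9, non-depressed | 3.13 item 3 | <5 |
| Two-week PHQ-9, non-depressed | 2.5.1 and 3.13 item 4 | <5 |

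**EF, step 1.** The conditions >40% and ≤40% cannot both hold, and together they cover every value. The group selected by 4.2 and the group meeting criterion 1 therefore have no member in common. Taken literally, none of the patients approached under 4.2 would satisfy criterion 1.

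**EF, step 2.** The sentence in 4.2 cannot be read as describing what happens to excluded patients, because the next sentence goes straight on to explaining the study and assessing eligibility.

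**EF, step 3: would a later step catch the error?** The 13-item screening list in 2.5.1 has no EF item, although the form tells the applicant to keep inclusion and exclusion criteria for 3.13 and 3.14. Section 4.6.1 does not list EF among the screening questions. Section 4.7.1 says the EF is recorded but gives no threshold. Before approach, the threshold thus appears only in 4.2 and 4.12, and these disagree. After approach there are two safeguards: the two-week call reconfirms eligibility (2.5.1), and randomisation follows only when all criteria are confirmed (2.6).

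**PHQ-9.** With whole-number scores starting at 0, <4 admits 0, 1, 2 and 3, and <5 admits 0, 1, 2, 3 and 4. The rules differ only at a score of exactly 4. Both apply to the inpatient screen, so the two-stage procedure does not explain the difference. The non-depressed cohort of the predecessor trial, described in section 1.3, also used below 5.

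**The case against.** The best defence is that both are slips the rest of the protocol resolves. Three sections agree on ≤40%, the trial is described throughout as one in systolic heart failure, and nurses would notice at once that nobody they approached qualified. Recruiters are also guided by a data-entry system and a screening script (4.6.3) that are not shown, so what they were actually given cannot be judged. A symbol misread when the PDF was converted cannot be wholly excluded either. Much of this stands, and it limits the harm. It does not make the sentence in 4.2 right.

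Three stronger readings are tempting and are not supported.

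- Section 4.12 cites 4.2, so a reader might infer that staff are sent to the wrong rule. But 4.12 states the EF gate itself, correctly, and cites 4.2 only for the screening that follows.
- A reader might infer that ineligible patients would be randomised. Section 2.6 requires every criterion to be confirmed first.
- A reader might take one admissible score out of five (0 to 4) to mean one patient in five. That counts scale values, not people, and the protocol gives no PHQ-9 distribution.

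On the PHQ-9 it is also fair to say that the stricter cut-off admits nobody whom 3.13 would exclude.

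**Conclusion.** Both contradictions are in the text and should be corrected. They are failures of internal consistency, not design choices, and their severity is moderate to low.

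The EF error is the more important. Read literally, it selects only patients who fail inclusion criterion 1. Its realistic cost is wasted or confused screening, and that depends on staff or the data system following 4.2 as written.

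The PHQ-9 error is minor. It concerns only inpatients scoring exactly 4 who are candidates for the non-randomised cohort of 125, and their number is unknown. Both co-primary hypotheses are comparisons between randomised arms, blended care against UC and against eUC, so that cohort does not enter them. Neither error alters the planned numbers or the randomised comparison.

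The conclusion assumes that the inequality sign in 4.2 was reproduced faithfully; a look at the source file would settle that.

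**What to change.** 1. In section 4.2, change the EF condition to ≤40%, to match 1.2, 3.13 item 1 and 4.12.
2. In section 2.5.1, change the first inpatient PHQ-9 cut-off from below 4 to below 5, to match 3.13 item 3 and the later text of 2.5.1.
3. Check the screening script and the eligibility logic of the data-entry system against 3.13 for both thresholds.

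The cost is two small text edits and one check of the script and form. Nothing in the design, sample size or analysis has to change.

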**4.7.1 If Yes, select the reason(s) for your request:**

Medical record review for ONLY the identification of potential subjects

**General Requirements: The Federal Policy [45 CFR 46.116 (d)] specifies in order for a waiver of consent to be approved, the request must meet four criteria. For each request, you will be asked to provide a justification addressing how each of these criterion is met.**

**Medical record review for the identification of potential subjects:**

|                                                                                                                                       |                                                                                                                                                                                                                                                                                                                                                                                                                                                                                                                                                                                                                                 |
|---------------------------------------------------------------------------------------------------------------------------------------|---------------------------------------------------------------------------------------------------------------------------------------------------------------------------------------------------------------------------------------------------------------------------------------------------------------------------------------------------------------------------------------------------------------------------------------------------------------------------------------------------------------------------------------------------------------------------------------------------------------------------------|
| The research involves no more than minimal risk to the subjects; [45 CFR 46.116 (d)(1)]                                               | The review of medical record information to determine eligibility poses no more than minimal risk to subjects since no changes will be made to patient care, and only those individuals who have clinical access will review records to determine eligibility. The research data (ejection fraction) will be entered in a password protected laptop into a password protected database that will be housed on a secure server of our Data Center. Records will be reviewed for eligibility only, and only by members of the research team who also has clinical access to the records, so patient privacy will not be violated. |
| The waiver or alteration will not adversely affect the rights and welfare of the subjects; [45 CFR 46.116 (d)(2)]                     | Records will be reviewed for eligibility only, and only by members of the research team who also has clinical access to the records, so patient privacy will not be violated.                                                                                                                                                                                                                                                                                                                                                                                                                                                   |
| The research could not practicably be carried out without the waiver or alteration; [45 CFR 46.116 (d)(3)]                            | The patients whose records will be viewed for eligibility are ill and hospitalized; we do not want to burden them by obtaining signed consent before it is clear that they are eligible for the first phase of screening.                                                                                                                                                                                                                                                                                                                                                                                                       |
| Whenever appropriate, the subjects will be provided with additional pertinent information after participation; [45 CFR 46.116 (d)(4)] | Eligible patients will be approached for consent to the larger study. Our study nurses will only confirm the percentage of their ejection fraction. Given the limited use of this Waiver, it is unlikely that pertinent information will be obtained.                                                                                                                                                                                                                                                                                                                                                                           |

